## Abstract

**Background:**

New research criteria for the diagnosis of Alzheimer’s disease (AD) have recently been developed to enable an early diagnosis of AD pathophysiology by relying on emerging biomarkers. To enable efficient allocation of health care resources, evidence is needed to support decision makers on the adoption of emerging biomarkers in clinical practice. The research goals are to 1) assess the diagnostic test accuracy of current clinical diagnostic work-up and emerging biomarkers in MRI, PET and CSF, 2) perform a cost-consequence analysis and 3) assess long-term cost-effectiveness by an economic model.

**Methods/design:**

In a cohort design 241 consecutive patients suspected of having a primary neurodegenerative disease are approached in four academic memory clinics and followed for two years. Clinical data and data on quality of life, costs and emerging biomarkers are gathered.

Diagnostic test accuracy is determined by relating the clinical practice and new research criteria diagnoses to a reference diagnosis. The clinical practice diagnosis at baseline is reflected by a consensus procedure among experts using clinical information only (no biomarkers). The diagnosis based on the new research criteria is reflected by decision rules that combine clinical and biomarker information. The reference diagnosis is determined by a consensus procedure among experts based on clinical information on the course of symptoms over a two-year time period.

A decision analytic model is built combining available evidence from different resources among which (accuracy) results from the study, literature and expert opinion to assess long-term cost-effectiveness of the emerging biomarkers.

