#### Emerging biomarker data

Biomarkers can be divided into two categories, one reflecting the presence of beta-amyloid protein (Aβ) and one reflecting neuronal degeneration or injury. A pathological cascade is hypothesized in which basically Aβ markers become abnormal first, followed by neuronal injury [9,44].

The biomarkers included in this project are outlined in Table 3. CSF is collected and Amyloid β42, total tau and phosphorylated-tau are analyzed using a standardized quantitative method. FDG uptake and Pittsburgh compound B binding (PiB) on PET are both qualitatively rated by a radiologist and quantitatively analyzed by standardized methods. Whole brain and hippocampal volume, white matter integrity and functional connectivity derived by MR imaging are quantitatively analyzed by a researcher. These tests are not part of the current routine clinical diagnostic procedure. They are judged and analyzed independently and blindly. The outcome of each test is dichotomous or continuous, both for AD aetiology and progression of cognitive decline.

**Table 3 T3:** Included biomarkers in the project categorized by reflecting Aβ or neuronal injury

**Technique**	**Aβ accumulation**	**Neuronal dysfunction**
CSF	Amyloid β42 in the CSF	total tau and phosphorylated-tau in CSF
PET	amyloid tracer uptake in PET	fluorodeoxyglucose PET
MRI		White matter integrity (DTI)
		Functional connectivity (rsfMRI)
		Whole brain volume
		Hippocampal volume

Abbreviations: Aβ, beta-amyloid protein; CSF, cerebrospinal fluid; DTI, diffusion tensor imaging; MRI, magnetic resonance imaging; PET, positron emission tomography; rsfMRI, resting state functional magnetic resonance imaging.

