### Analyses

Several diagnostic procedures based on current practice and emerging biomarker information (index tests) are compared to the reference diagnosis. First, AD aetiology based on the core clinical criteria [7,8] is evaluated. This is reflected by the baseline diagnosis as determined by the consensus procedure. No information of any emerging biomarker is included. Second, AD aetiology based on the research criteria as established by the National institute on aging and the Alzheimer’s Association are evaluated [9]. At last, several explorative decision rules are applied including clinical information and biomarker information to determine AD aetiology and suspected progression of cognitive decline within two years.

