#### Research goal 1: Diagnostic test accuracy

Diagnostic test accuracy is determined by relating index test results to the reference diagnosis (reference test). All diagnoses consist of a dichotomous outcome value on underlying pathology of the clinical syndrome and on (expected) progression of cognitive decline within two years. Separately for aetiology and progression of cognitive decline each index test result for each case is indicated as either true positive, true negative, false positive or false negative based on the reference diagnosis (reference test). This enables the calculation of accuracy estimates: sensitivity, specificity, positive predictive value, negative predictive value, likelihood ratio and (an increase of) the Area Under the Curve of a Receiver Operating Characteristic curve.

Finally, novel innovative diagnostic tests are developed during the course of this study by other cooperating researchers for which proof of principle does not yet exist. These tests will be evaluated as soon as evaluation in clinical subjects is possible. To assess diagnostic accuracy the tests will be applied in subgroups of the cohort retrospectively (for CSF samples) or using a case–control design.

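### The current-practice comparator is an expert verdict and the biomarker strategies are decision rules, so a difference in accuracy mixes the biomarkers' contribution with the change from judgement to rule

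*Protocol article*

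**What the plan says.** Two kinds of index test are set against the reference diagnosis.

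- **Current practice.** The abstract states: "The clinical practice diagnosis at baseline is reflected by a consensus procedure among experts using clinical information only (no biomarkers". The Analyses section repeats this for the core clinical criteria: "This is reflected by the baseline diagnosis as determined by the consensus procedure".
- **Biomarker strategies.** For the research criteria the abstract states: "The diagnosis based on the new research criteria is reflected by decision rules that combine clinical and biomarker information". The Analyses section adds a further, exploratory family: "several explorative decision rules are applied including clinical information and biomarker information to determine AD aetiology".

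The section on the baseline and reference diagnoses makes the reference an expert consensus too. It rests on the two-year clinical course and the core clinical criteria, with the experts blind to the biomarkers.

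On scale, Research goal 1 states: "All diagnoses consist of a dichotomous outcome value on underlying pathology of the clinical syndrome". The same requirement covers progression, and every index test result is classed as a true or false positive or negative. That section's list of accuracy measures nevertheless ends with "likelihood ratio and (an increase of) the Area Under the Curve of a Receiver Operating Characteristic curve", without saying what the increase is measured from. The section on emerging biomarker data says of the single tests: "The outcome of each test is dichotomous or continuous, both for AD aetiology and progression of cognitive decline".

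Research goal 2 divides the change in costs by the change in accuracy between current practice and the biomarker procedures. Research goal 3 carries each procedure's proportions of correct and incorrect diagnoses into the model.

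**The concern.** Two things change together between the strategies being compared: biomarker information is added, and expert judgement gives way to a rule. The article names neither a rule on clinical data alone nor an expert verdict with biomarkers, so the stated contrast cannot separate the two changes.

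Goal 1 asks about the accuracy of emerging biomarkers, and the study exists to inform their adoption. If a rule applied to the clinical data alone would already beat the panel, the biomarkers are credited with a gain they did not produce. If the rule uses the clinical data less well than the panel does, a useful biomarker can look worthless. Either error passes into the cost per correct diagnosis and the long-term model.

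A separate and conditional question concerns AUC. A yes/no verdict gives one point on the ROC curve and a graded score gives a whole curve, so comparing their areas can show a gain without any new information.

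**Working it through.** **Benchmark.** The sample size section takes 80% accuracy for current practice (70% in non-demented patients), a relevant difference of 10 points, α = 5%, 10% drop-out and 219 patients. I read the printed β of 80% as 80% power and α as two-sided. For 80% against 90%, the unpooled two-proportion formula gives (0.80×0.20 + 0.90×0.10) × (1.960 + 0.842)² / 0.10² = 196.2, rounded up to 197. Then 197 / 0.9 = 218.9, that is 219. The figure reproduces, and the 10-point benchmark is a difference in accuracy, not in AUC.

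**What differs between the strategies.**

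| Index test | Information | How it is combined | Output |
|---|---|---|---|
| Current practice | clinical | expert consensus | yes/no |
| Research criteria | clinical + biomarker | decision rule | yes/no |
| Exploratory rules | clinical + biomarker | decision rule | yes/no |

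The second and third columns change together; the last does not. A continuous marker inside a rule that ends in a yes/no diagnosis is on the panel's scale. Accuracy, sensitivity, specificity and the predictive values therefore carry no scale artefact.

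**Size of the change of method (assumptions mine).** The documents do not allow this to be computed. As an illustration, suppose that sensitivity equals specificity equals accuracy, that the panel's verdict contains random decision noise with variance r times the marker variance, and that a rule uses the same clinical data without noise. Then:

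rule accuracy = Φ( z(panel accuracy) × √(1 + r) )

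| Panel accuracy | r = 0.10 | r = 0.25 | r = 0.50 |
|---|---|---|---|
| 80% | 81.1% | 82.7% | 84.9% |
| 70% | 70.9% | 72.1% | 74.0% |

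The change of method is then worth about 1 to 5 points with no biomarker effect. This model can only favour the rule. A rule that uses the clinical data less well than the panel would move the result the other way. So could the reference, which shares its consensus method and clinical criteria with the comparator.

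**Size of the AUC artefact, if it arises.** Assume an equal-variance binormal score and identical information on both sides.

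- Verdict: AUC = (sensitivity + specificity) / 2.
- Score: AUC = Φ( (z(sensitivity) + z(specificity)) / √2 ).

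| Sensitivity / specificity | Verdict | Score | Difference |
|---|---|---|---|
| 0.80 / 0.80 | 0.800 | Φ(1.683/1.414) = 0.883 | +0.083 |
| 0.70 / 0.70 | 0.700 | Φ(1.049/1.414) = 0.771 | +0.071 |
| 0.90 / 0.70 | 0.800 | Φ(1.806/1.414) = 0.899 | +0.099 |

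Over all cases tried the difference ran from 0.057 to 0.099. It is zero if both sides are scored yes/no.

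**The case against.** The strongest defence is that the contrast is the intended one. The Background asks for the value of strategies that include biomarkers compared with current practice, and Research goal 2 compares exactly these. For an adoption decision, expert practice is the relevant comparator, and a clinical-only algorithm may be something nobody uses. This stands as a reason to keep the contrast. It does not license crediting the whole difference to the biomarkers.

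A second defence is that the exploratory rules are not itemised. A clinical-only rule may be described elsewhere, and the rules may already take the panel's diagnosis as their clinical input. That is possible. The point is confined to the contrasts that the article states, and in these the two changes coincide.

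Three stronger readings are tempting, and the documents do not support them:

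- A reader might infer that the accuracy gain also mixes in a change of scale. Research goal 1 rules this out by making all diagnoses dichotomous.
- A reader might infer that a rule no better than the panel is bound to show an AUC gain. That needs a continuous score set against the yes/no verdict. The article describes single tests as possibly continuous and leaves the baseline of the AUC increase open, so it allows this comparison but does not state it. The increase could equally mean a clinical model with and without a marker.
- A reader might infer a known bias in favour of the biomarkers. The consensus reference may favour the panel, so the net direction is open.

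**Conclusion.** The point holds for the method of diagnosis. As stated, the comparison cannot attribute a difference in accuracy to the biomarkers, and that difference feeds the economic results. Its size and direction cannot be obtained from the documents; the 1 to 5 points rest on assumed noise fractions and a noise-free rule.

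For accuracy, sensitivity and specificity there is no scale artefact. For AUC there is a conditional one, about 0.07 to 0.08 at 0.70/0.70 and 0.80/0.80 under the binormal assumption. It should not be read against the 10-point benchmark, which is on a different measure. The design and the data collected are not in question; what is needed is an added analysis and a clear statement of what the AUC increase compares.

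**What to change.** 1. Keep panel against rule as the strategy comparison for the economic evaluation, and label it as such.
2. For each exploratory biomarker rule, run the same rule on the same patients with the biomarker terms left out. Report the paired difference as the biomarkers' added value.
3. For the research criteria, hold the panel's baseline clinical diagnosis as the clinical input, so that only the biomarker input changes.
4. Compute any increase in AUC only between scores on the same scale. Compare rules with the panel's verdict on sensitivity and specificity at a fixed cut-off.

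The cost is a little more analysis on data already being collected and a few lines of text. The gain credited to biomarkers may turn out smaller.

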**Discussion:**

Several other multi-centre trials study the relative value of new biomarkers for early evaluation of AD and related disorders. The uniqueness of this study is the assessment of resource utilization and quality of life to enable an economic evaluation. The study results are generalizable to a population of patients who are referred to a memory clinic due to their memory problems.

**Trial registration:**

NCT01450891

## Background

Alzheimer’s disease (AD) and other dementing disorders are common in the elderly, with a worldwide prevalence estimated in 2010 at 35.6 million, which will double every 20 years to 115.4 million in 2050. AD has a substantial impact on the person who suffers from the disease, his or her family and society [1]. AD affects a person’s cognition, behavior and functional ability, and it is one of the leading causes of disability in older people living in developed countries [2].

The NINCDS-ADRDA criteria [3] are currently applied in diagnostic guidelines [4,5] to determine AD aetiology. Scientific knowledge, advanced imaging techniques and cerebrospinal fluid analyses have evolved since the publication of these criteria in 1984. This has led to much debate and the proposition of new clinical and research criteria to enhance diagnostic accuracy, even at the stage of early clinical symptoms [6-10]. These criteria distinguish between the AD pathophysiological process and the clinically observable syndrome to enable determination of AD in a pre-dementia state; e.g. mild cognitive impairment (MCI). In the end the criteria are meant to support therapy decision making (when effective treatments are available) or to determine the likelihood of cognitive and functional progression to a more severe disease state. Emerging biomarkers are attributed a more prominent role in the diagnostic criteria; amyloid β42, total tau and phosphorylated-tau in the cerebrospinal fluid (CSF), amyloid tracer uptake and fluorodeoxyglucose (FDG) in positron emission tomography (PET), hippocampal volume and medial temporal atrophy in structural magnetic resonance imaging (MRI) and single photon emission tomography (SPECT) perfusion imaging. However, validation of the criteria is needed before adoption of the proposed role of new biomarkers in clinical practice [9].

The ultimate goal of diagnostic testing is to guide disease management in order to improve patient outcomes and patient well-being. Tests that lack this potential should be regarded obsolete [11,12]. This has raised an urgent need for health technology assessment to address the direct, intended consequences of technologies as well as the indirect, unintended consequences for the evaluation of the value of diagnostic strategies including biomarker for AD compared to current clinical practice. Evidence is needed to support decision makers on the adoption of new diagnostic tests in clinical practice to enable efficient allocation of health care resources.

## Study aim

The general aim of the study is to assess the clinical and economic value of current, emerging and novel (to be developed) techniques for an early diagnosis of AD and related disorders. In this paper the methodology is described.

The research goals are:

1. To assess the diagnostic test accuracy of the current clinical standard diagnostic work-up and emerging diagnostic biomarkers in MRI, PET and CSF

2. To assess costs and effects for the follow-up period to perform a cost-consequence and cost-effectiveness analysis

3. To develop a preliminary economic model to assess the uncertainty surrounding long-term cost-effectiveness of diagnostic strategies

## Methods/design

### Study design

A cohort design was chosen because an assessment of test combinations within a randomized controlled trial would require the evaluation of many diagnostic strategies for which the number of subjects needed would exponentially increase [13]. To determine the diagnostic value of emerging biomarkers for AD and related disorders both a clinical diagnosis and diagnosis based on emerging biomarkers (index tests) are compared with a reference diagnosis. Due to limited ability of biopsy (which is unethical) or autopsy (which requires follow up until death) a two-year follow up of the clinical course is used as a proxy to obtain information on the state of the disease at baseline; so-called delayed-type cross-sectional accuracy study design [12]. Four academic memory clinics (Leiden University Medical Centre, Maastricht University Medical Centre, Radboud University Nijmegen Medical Centre and VU University Medical Centre) specialized in the diagnosis and treatment of memory disorders participate in the study. Two memory clinics are settled within a department of geriatrics, one within neurology and one within psychiatry. The study is performed within the framework of CTMM, the Center for Translational Molecular Medicine (http://www.ctmm.nl), a Dutch public-private partnership; project LeARN (grant 02 N-101).

### Subjects

For the study, 241 consecutive patients of the participating memory clinics who were suspected of having a primary neurodegenerative disease were included for participating in the study from October 2009 to May 2011; this included all patients with subjective and/or objective memory complaints. Eligibility criteria were chosen to represent the current clinical situation and enable generalisability to clinical practice (see Table 1). Informed consent was obtained from both the patient and the informal caregiver. Gender, age and reason for refusal were obtained for patients unwilling to participate.

**Table 1 T1:** Eligibility criteria for subject selection

*Inclusion criteria*	
-	All new consecutive patients of the participating memory clinics who are suspected of having a primary neurodegenerative disease
-	Mini-Mental State Examination: ≥ 20
-	Clinical Dementia Rating: 0 – 1
-	Availability of a reliable informer or proxy (who visits or contacts the patient at least once a week)
*Exclusion criteria*	
-	Normal Pressure Hydrocephalus, Huntington’s disease
-	Less than two years ago a transient ischaemic attack (TIA) or cerebral vascular accident (CVA) or TIA/CVA followed (within three months) by cognitive impairment
-	Psychiatric history (schizophrenia, bipolar disorder or psychotic problems (not otherwise specified), less than 12 months ago)
-	Major Depression according to the DSM-IV, less than 12 months ago
-	Cognitive problems due to excessive alcohol use (based on clinical judgement)
-	Brain tumour, epilepsy, encephalitis
-	Probably not available for follow-up

### Data assessment

Each centre collects a minimum dataset of clinical information based upon the dataset protocol used for The String of Pearls Initiative – Pearl Neurodegenerative Diseases (http://www.string-of-pearls.org), cost data and data on emerging biomarkers. Table 2 provides an overview of all patient and informal caregiver assessments. Assessments take place at baseline and at 12 and 24 months follow up during a visit (from both patient and informal caregiver) to the memory clinic. Furthermore, several questionnaires were composed in a booklet to measure resource consumption and quality of life. This is filled out by the informal caregiver at baseline, 3, 12 and 24 months.

**Table 2 T2:** Overview of patient and informal caregiver assessments at baseline and follow-up

**Outcome measure**	**Operationalization/type of instrument**	**B**	**T3**	**T12**	**T24**
***Clinical data***					
Demographic data	History taking	P		P	P
Cognitive impairment	Mini-mental State Examination	P		P	P
Dementia severity	Clinical Dementia Rating	P		P	P
Functional disability	Disability Assessment for Dementia	P		P	P
Neurological and physical examination	Neurological assessment and evaluation of co-morbidities	P		P	P
Neuropsychiatric problems	Neuropsychiatric Inventory	P		P	P
Depression	Geriatric Depression Scale 15	P		P	P
Cerebral atrophy and white matter lesions	Structural MRI (T1-weighted, T2-weighted and FLAIR)	P			
Neuropsychological Assessment	Rey’s Verbal Learning Test, Visual Association Test, Digit-Span, Letter Digit Substitution Test, Stroop Color-Word Test, Trail Making Test	P		P	P
***Quality of life data***					
Patient generic quality of life	EQ-5D	I*/P	I*	I*/P	I*/P
Patient disease specific quality of life*	QoL-AD	I *	I *	I *	I *
Caregiver generic quality of life*	EQ-5D	I	I	I	I
Caregiver disease specific quality of life*	QoL-AD	I	I	I	I
Caregiver burden*	Sense Of Competence	I	I	I	I
Care-related quality of life*	Carer Quality of Life	I	I	I	I
***Cost data****					
Resource utilization and caregiver time	RUD-Lite	I	I	I	I
Work productivity and absence	Productivity and Disease Questionnaire	I	I	I	I
Consequences of informal caregiving on paid or unpaid work	Health and Labour Questionnaire	I	I	I	I
Other resource use		I	I	I	I
***Emerging biomarker data***					
Functional connectivity	Resting state functional MRI	P			
White matter integrity	Diffusion tensor imaging	P			
Hippocampal volume	Structural MRI	P			
Glucose metabolism	Fluorodeoxyglucose PET†	P			
Amyloid plaque deposition	Pittsburgh compound B PET†, CSF Aβ1-42	P			
Tau	CSF total tau, CSF phosphorylated tau	P			

*These items were assessed by the informal caregiver by means of a booklet in which several questionnaires were composed for resource consumption and quality of life.

†Data on this item are only collected at the memory clinic of the VU University Medical Centre Amsterdam.

Abbreviations: B, Baseline; FLAIR, Fluid attenuation inversion recovery; I, Information retrieved from informal caregiver; MRI, Magnetic Resonance Imaging; P, Information retrieved from patient; PET, positron emission tomography; QoL-AD, Quality of Life Alzheimer’s Disease scale; RUD-Lite, Resource Utilization In Dementia; T3, 3 month follow-up measurement; T12, 12 month follow-up measurement; T24, 24 month follow-up measurement.

